### Safety assessment and adverse event reporting

Safety will be assessed by recording all adverse events (AEs), serious adverse events (SAEs), and predefined major adverse cardiovascular events (MACEs). Any treatment discontinuation or modification related to an adverse event will be documented. Laboratory tests, including hematology, liver function, and renal function, as well as vital signs and 12-lead electrocardiography, will be performed at baseline and week 12, with additional assessments as clinically indicated. Adverse event severity will be graded according to CTCAE version 5.0. Potential MACEs will be reviewed by an independent clinical endpoint committee.

### Follow-up, discontinuation, withdrawal, and data management

Eligible participants will be identified on the basis of stress MCE findings during the screening period, with confirmation of CMVD requiring evidence of reduced myocardial perfusion or perfusion defects. Following enrollment, participants will attend onsite visits at week 0 (baseline), week 8 (±7 days), and week 12 (±7 days). Comprehensive efficacy assessments, including the CPET, laboratory tests and safety evaluations, will be conducted at both the baseline visit and the week 12 visit. The week-8 visit will focus on adherence, review of concomitant medication, symptom and patient-reported outcome assessment, and interim safety monitoring (Table 1). Stress MCE is performed only at screening for diagnostic confirmation and is not repeated during follow-up.

**Table 1 T1:** Schedule of assessments and data collection time points for the hybrid study.

Period	Screening period	Pretreatment	Treatment period	Treatment period	Follow-up period
	−1 week	0 week	8 weeks	12 weeks	16 weeks
Baseline information					
Informed consent	√				
Eligibility screen	√				
Demographics and medical history	√				
Physical examination and vital Signs	√			√	
Randomization					
Diagnostic confirmation					
Stress MCE	√				
Outcome measurements					
CPET	√			√	
Echocardiography (Conventional Parameters) and ECG	√				
Laboratory tests(lipid profile, HCY, hs-CRP)	√			√	
SAQ	√		√	√	
Health questionnaires (PHQ-9, GAD-7)	√			√	
Chinese medicine symptom scoring scale	√			√	
Safety assessments					
Liver function	√			√	
Renal function	√			√	
Adverse events			√	√	√
MACEs			√	√	√
Others					
Concomitant medication record	√	√	√	√	
Evaluate compliance			√	√	

HCY, homocysteine; hs-CRP, high-sensitivity C-reactive protein; SAQ, seattle angina questionnaire; PHQ-9, health questionnaire depression scale; GAD-7, generalized anxiety disorder scale; ECG, electrocardiogram; MCE, myocardial contrast echocardiography; CPET, cardiopulmonary exercise testing; MACEs, major adverse cardiovascular events.

“√” represents the need for implementation at this point in time.

Participants may discontinue study treatment because of voluntary withdrawal, pregnancy, hypersensitivity reactions, or adverse events related to the study drug and requiring treatment cessation. When feasible, study staff will attempt to collect end-of-treatment outcome data. For participants who drop out or are lost to follow-up, repeated contact attempts by telephone, written notice, or other approved methods will be made and documented. All the data collected before discontinuation are retained for auditing. The most recent available assessments, including primary endpoint data when available, will be handled according to the prespecified statistical analysis plan.

All study data will be entered into an electronic case report form (eCRF) via the Weiyun Clinical Research Integrated Platform (v3.0; http://we.ttdoc.cn/sp). Double data entry and programmed edit checks will be used to ensure data quality. Audit trials and role-based access control will also be applied.

### Data collection and management

Before trial initiation, all study personnel, including investigators, coordinators, sonographers, CPET technicians, and data managers, will receive standardized training on the protocol, standard operating procedures (SOPs), and good clinical practice (GCP). To minimize inter-center variability, all sites will adhere to the same acquisition protocol. Centralized training and periodic quality audits will be conducted. CPET calibration and analysis will be centrally reviewed. Statistical models will include site as a random effect to account for potential clustering. The training will focus on harmonized stress MCE acquisition, including contrast administration, imaging settings, destruction–replenishment sequences, and timing under regadenoson; standardized CPET procedures, including calibration, incremental protocols, termination criteria, and quality indicators such as the respiratory exchange ratio (RER); and consistent documentation of endpoint-related variables to ensure comparability across study sites.

All study data will be entered into an electronic case report form (eCRF) system with role-based access control. Double data entry will be performed by two independent staff members, and any discrepancies will be resolved by source data verification. Built-in range checks and programmed logic rules will be applied to key variables—including MCE-derived diagnostic confirmation (CFR <2.0), CPET parameters (peak VO₂ and quality indicators), patient-reported outcome scores, visit windows, and medication changes—to minimize transcription errors and ensure data completeness.

To maintain data integrity in this multicenter study, qualified monitors will perform periodic risk-based quality control reviews, including onsite monitoring, remote verification, and regular communication with site teams. Monitoring will assess data completeness, timeliness, logical consistency, and agreement with source documents. Queries are issued through the eCRF system, tracked until resolution, and documented in the audit trail.

Imaging and physiologic data will undergo centralized quality control. All MCE DICOM files will be anonymized at each site, transferred securely to a blinded core laboratory, and analyzed according to prespecified rules. A random 10% sample will be reread to assess interobserver and intraobserver variability. CPET raw files, including calibration logs, peak effort criteria such as RER, and protocol adherence, will be archived and centrally reviewed for quality. For the nested AI study, imaging datasets are deidentified and stored separately from clinical identifiers, and the linkage keys are retained only at the coordinating center.

All study data will be stored in an encrypted electronic environment with restricted access. Personally identifiable information and imaging data receive additional protection through encryption and limited access. Full audit trials will be maintained. Data handling will comply with the Declaration of Helsinki, applicable ethical requirements, and relevant data protection regulations to protect participant privacy and data security.

### Data monitoring committee

Given the low-risk profile of the interventions and the lack of planned interim analyses, a formal data monitoring committee (DMC) will not be convened. Safety oversight will be provided by the sponsor's quality assurance unit through periodic risk-based monitoring, with serious adverse events reviewed promptly. An independent external safety advisor may be consulted if clinically important safety concerns arise.

### Dissemination policy

Trial results will be submitted for publication in a peer-reviewed journal regardless of outcome direction. The participants will receive a lay-summary of findings. Authorship will follow ICMJE guidelines; no professional writers will be used. The full protocol, anonymized participant-level dataset, and statistical code will be available upon reasonable request to the corresponding author.

### Data access

Access to the final trial dataset will be limited to the principal investigators, study coordinators, and independent statistician. No contractual agreements restrict investigator access. De-identified data will be shared with external researchers upon reasonable request after publication, subject to approval by the study steering committee and applicable data protection regulations.

### Statistical analysis

All analyses will be prespecified. The primary analysis will be conducted in the intention-to-treat (ITT) population, including all randomized participants analyzed according to their assigned group. A per-protocol (PP) analysis will be performed as a sensitivity analysis.

Baseline characteristics will be summarized via descriptive statistics. Continuous variables are presented as the means ± SDs if approximately normally distributed or medians (IQRs) otherwise; categorical variables are reported as *n* (%). Normality will be assessed via graphical methods and formal tests (e.g., Shapiro-Wilk).

#### Primary endpoints

The primary endpoint is the change in peak VO_2_ measured by CPET from baseline to week 12. The primary analysis will be performed via an analysis of covariance (ANCOVA) model, with the treatment group as a fixed effect and the corresponding baseline value as a covariate. The study center will be included either as a fixed effect or as a random effect in a mixed-effects model, depending on model fit and the distribution of participants across centers. The results are reported as adjusted mean differences with 95% confidence intervals and two-sided *P* values.

#### Secondary outcomes

Continuous secondary outcomes—including laboratory parameters, patient-reported outcome scores, and CPET indices other than peak VO_2_—will be analyzed as changes from baseline via ANCOVA with baseline adjustment. If distributional assumptions are violated, rank-based ANCOVA or nonparametric methods (e.g., the Mann–Whitney *U*-test) will be applied. Categorical outcomes will be compared via the chi-square test or Fisher's exact test, as appropriate. Exploratory analyses will assess correlations between changes in peak VO_2_ and improvements in symptoms or quality of life (e.g., SAQ scores) via Pearson or Spearman coefficients. Safety outcomes, including adverse events, major adverse cardiovascular events, and changes in liver and renal function, will be summarized descriptively and compared between groups where applicable.

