#### Secondary outcomes

The secondary outcomes will be assessed at baseline and week 12 and will include the following:
**Biomarkers:** lipid profile, homocysteine (HCY), high-sensitivity C-reactive protein (hs-CRP);**CPET parameters:** additional functional indices as described above;**Symptoms and patient-reported outcomes:** Seattle Angina Questionnaire (SAQ) score, Chinese medicine symptom scoring scale, and visual analog scale (VAS);**Psychological status:** Patient Health Questionnaire-9 (PHQ-9) and Generalized Anxiety Disorder-7 (GAD-7);**Quality of life:** EuroQol Five-Dimension scale (EQ-5D).All scale-based assessments will be independently completed by two physicians with at least 5 years of clinical experience, and any disagreements will be resolved by consensus.

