#### Missing data

Missing primary endpoint data at week 12 will be handled via multiple imputation under the missing-at-random assumption. Sensitivity analyses will include complete-case analysis and other prespecified approaches when needed, such as pattern-mixture models or conservative imputation methods.

All the statistical tests will be two-sided. The overall two-sided significance level for the primary endpoints will be set at *α* = 0.05 after adjustment for multiplicity. Analyses will be performed via SPSS (v26.0) and/or validated statistical software (e.g., SAS/R) as specified in the SAP.

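### SAQ is scheduled at week 8, but the outcome list omits that visit and the stated analysis gives it no role, a modest loss of robustness for one secondary outcome

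*Protocol article*

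**What the plan says.** **Collection.** Table 1 marks SAQ at screening, week 8 and week 12. The text of Follow-up, discontinuation, withdrawal, and data management agrees: "The week-8 visit will focus on adherence, review of concomitant medication, symptom and patient-reported outcome assessment".

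**Outcome definition.** Outcomes, Secondary outcomes, gives different time points: "The secondary outcomes will be assessed at baseline and week 12". SAQ stands there beside the other symptom scales, with no ranking and no mention of week 8.

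**Analysis.** Statistical analysis, Secondary outcomes, says that continuous secondary outcomes, expressly including patient-reported scores, "will be analyzed as changes from baseline via ANCOVA with baseline adjustment". It names no visit term and no repeated-measures model.

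**Missing data.** The only stated rule concerns the primary endpoint: "Missing primary endpoint data at week 12 will be handled via multiple imputation under the missing-at-random assumption". No rule is given for secondary outcomes. The follow-up section leaves the handling of last available assessments to the SAP, which is not shown.

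**The concern.** Participants are asked for an SAQ at week 8, yet the article gives that score no stated use. An ANCOVA of the baseline-to-week-12 change, with no imputation, can only use people who have a week-12 score. Someone who attends week 8 and then leaves would be left out of the SAQ comparison although a recent score is on file.

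Two things are at stake. One is a little precision. The other is robustness: if people leave because of how they felt at week 8, and this happens more in one arm, those who remain are no longer comparable between arms, and the week-8 score is the information that could correct for it. There is also a smaller point of definition. While the outcome list and the schedule disagree, it is not settled whether week 8 is an SAQ outcome time point, and this is better settled before the data are seen.

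**Working it through.** **Inputs from the protocol.** Target 50 per arm, 15% attrition, 1:1 allocation. The attrition step reproduces: 42 / 0.85 = 49.41, rounded up to 50. These figures were set for peak VO₂; the protocol gives no figure for SAQ.

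**Assumptions.** The protocol does not give these, so ranges are used:
- ρ, the correlation of week-8 with week-12 SAQ given baseline: 0.5 to 0.8.
- q, the share of those lacking week 12 who do have week 8: 0.25 to 1.
- Attrition of 15% applies to SAQ equally in both arms.

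**Step 1, how many are affected.** 0.15 × 50 = 7.5 per arm, or 15 of 100, would lack a week-12 SAQ, leaving m = 42.5 per arm. Of the 7.5, only 7.5q have a week-8 score that can be used.

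**Step 2, precision.** With N = 42.5 + 7.5q, the variance of the week-12 mean using week 8, relative to week-12 completers only, is (1 − ρ²) + ρ² × m/N.

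| ρ | q | N | Relative variance | Effective n per arm | SE reduction |
|---|---|---|---|---|---|
| 0.5 | 0.25 | 44.375 | 0.75 + 0.25 × 42.5/44.375 = 0.989 | 43.0 | 0.5% |
| 0.7 | 0.5 | 46.25 | 0.51 + 0.49 × 42.5/46.25 = 0.960 | 44.3 | 2.0% |
| 0.8 | 1 | 50 | 0.36 + 0.64 × 42.5/50 = 0.904 | 47.0 | 4.9% |

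The gain is about 0.5 to 4.5 effective participants per arm.

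**Step 3, bias if dropout follows the week-8 score in one arm only.** Take no true effect, 15% missing in each arm, random in one arm and dependent on week 8 in the other. The bias, in SDs of the week-12 score given baseline, is ρ times the shift in the mean week-8 score among those who stay.
- Moderate dependence (odds of leaving change by a factor e per SD): shift 0.133. Bias is 0.5 × 0.133 = 0.07, 0.7 × 0.133 = 0.09 and 0.8 × 0.133 = 0.11.
- Extreme case (the lowest-scoring 15% all leave): shift 0.233 / 0.85 = 0.274. Bias is 0.14, 0.19 and 0.22 at the same ρ.

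A separate simulation had 50 per arm, a standardized effect of 0.5, a baseline correlation of 0.5 and placebo dropout depending on week 8. It gave completer bias of −0.063, −0.084 and −0.099 SD at week-8/week-12 correlations of 0.6, 0.7 and 0.8, against about 0 when week 8 was used. The two together give the range of roughly 0.06 to 0.11 SD for moderate dependence.

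**Step 4, scale.** On the units of Step 3, the SE of the arm difference with 42.5 per arm is √(2/42.5) = 0.217. A bias of 0.07 to 0.11 is therefore about 0.07/0.217 = 0.3 to 0.11/0.217 = 0.5 of one standard error.

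**The case against.** The strongest reply is that the SAP may already deal with this. The follow-up section defers the handling of last available assessments to it, in wording that reaches beyond the primary endpoint, and an ANCOVA is compatible with imputation that draws on week 8. This stands. A reader might infer that the plan excludes everyone without a week-12 SAQ, but no sentence says so; it is only what follows from the stated model if nothing is added. What the deferral does not settle is the mismatch in time points, or that the article does fix a model for these scores and confines its stated imputation to the primary endpoint.

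A second reply is that leaving treatment is not the same as having no data. Staff will try to obtain end-of-treatment outcomes and will make repeated contact attempts. This also stands. It would be too strong to say that every early leaver's week-8 score is thrown away: some will still give a week-12 SAQ, and those who leave before week 8 have no such score.

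Third, an ANCOVA at the final visit is a standard and valid analysis, and the bias appears only when dropout is assumed to depend on week 8 differently in the two arms. That is right, and the remedy has the matching limit: if people leave because symptoms worsen after week 8, a model using week 8 is biased too.

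Fourth, the outcome list can be read as naming the endpoint visit, with week 8 as an intermediate visit. That reading is possible, but the text does not say it.

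**Conclusion.** The point holds as a low-cost improvement, not as an error in the analysis. The schedule and the outcome list differ on week 8, and the stated method gives the week-8 SAQ no role. Subject to the SAP, participants with week 8 but not week 12 would add nothing to the SAQ comparison.

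The precision gain from using week 8 is small, about 0.5% to 5% of the standard error, and depends on the assumed ρ and q. The bias of roughly 0.06 to 0.11 SD is conditional on dropout that follows the week-8 score and differs by arm, for which the protocol offers no evidence either way. Its removal relies on a correctly specified model under missing-at-random, the assumption the protocol already makes for peak VO₂.

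A reader might take SAQ to be the main symptom outcome. The protocol does not rank it: it is the only efficacy scale marked at week 8 and the named example for the exploratory correlation with peak VO₂, but that is not a ranking. The primary endpoint and the sample size are untouched.

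**What to change.** In Outcomes, Secondary outcomes, list week 8 as a time point for SAQ so that it agrees with Table 1, and say that week 12 is the time point of interest.

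Then state one of two analyses, in the protocol or the SAP:
- A mixed model for repeated measures on SAQ at weeks 8 and 12, with arm, visit, arm-by-visit interaction and baseline SAQ, and site handled as for the primary endpoint. Report the week-12 contrast as the secondary result.
- The present ANCOVA at week 12, with multiple imputation extended to SAQ and the week-8 score as an auxiliary variable.

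If the SAP already does either, a cross-reference and the corrected time points are enough.

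The cost is wording, slightly more modelling work and reliance on missing-at-random. No extra data are needed. The trial is still recruiting, so the choice can be fixed before database lock.

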### Randomization and allocation concealment

The participants will be randomized at a 1:1 ratio through a centralized web-based system managed by the Clinical Trial Management Office of Guangdong Provincial Hospital of Traditional Chinese Medicine. A site-stratified block randomization sequence will be generated via SAS (v9.4; SAS Institute Inc.). Allocation concealment will be ensured through centralized drug coding. Center identifiers, randomization numbers, subject identification numbers, and medication codes will be maintained by an independent statistical unit.

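### The fallback for non-normal secondary outcomes allows a Mann–Whitney test that adjusts for neither baseline nor site, giving up power that the rank-based ANCOVA named beside it would keep

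*Protocol article*

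**What the plan says.** Under Statistical analysis, Secondary outcomes, continuous secondary outcomes (laboratory parameters, patient-reported scores, CPET indices other than peak VO₂) "will be analyzed as changes from baseline via ANCOVA with baseline adjustment". The next sentence gives the fallback: "If distributional assumptions are violated, rank-based ANCOVA or nonparametric methods", the second branch being illustrated by the Mann–Whitney U-test. Nothing says which branch applies to which outcome. Change from baseline is the only analysis variable named, so the natural reading is that Mann–Whitney would be run on change.

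Site enters in three other places. Randomization and allocation concealment: "A site-stratified block randomization sequence will be generated via SAS". Data collection and management: "Statistical models will include site as a random effect to account for potential clustering". Primary endpoints, for peak VO₂ only: "The study center will be included either as a fixed effect or as a random effect in a mixed-effects model". The secondary-outcome ANCOVA does not itself mention site.

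**The concern.** The fallback sentence treats two unlike procedures as interchangeable. Rank-based ANCOVA deals with non-normality and still uses the baseline value, and it can take the site stratum as a further term. Mann–Whitney on change takes no covariate and no stratum. It subtracts the baseline, which is not the same as adjusting for it: when the baseline to week-12 correlation is below one, subtraction over-corrects and leaves avoidable noise in the comparison. It also gives no adjusted estimate.

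The outcomes most likely to take this route are skewed biomarkers such as hs-CRP and homocysteine. At stake is the sensitivity of those comparisons in a trial of 84 evaluable participants, where the better alternative already stands in the same sentence.

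**Working it through.** **Inputs from the protocol.** 42 evaluable per group, allocation 1:1, α = 0.05 two-sided, six named sites. No power is stated for any secondary outcome, and no baseline to week-12 correlation is given for anything.

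**The plan's own figure.** For the primary endpoint, Δ = 4.71 and σ = 6.5. The noncentrality is (4.71/6.5) × √(42/2) = 0.7246 × 4.583 = 3.32 on 82 degrees of freedom. The noncentral t then gives 90.68% power, exactly as stated. Inflation for dropout, 42/0.85 = 49.41, gives 50. So 42 per group is a fair basis for the rest. (The printed formula yields 40.04 rather than the 41.5 shown; this does not bear on the present point.)

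**Why adjustment matters.** With common variance σ² and correlation ρ, change has variance 2(1−ρ)σ², and the ANCOVA residual has variance (1−ρ²)σ². The efficiency of an unadjusted test on change is therefore (1−ρ²)/[2(1−ρ)] = (1+ρ)/2. For Mann–Whitney under normality, multiply by 3/π:

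- ρ = 0.5: 0.75 × 0.955 = 0.72
- ρ = 0.7: 0.85 × 0.955 = 0.81
- ρ = 0.8: 0.90 × 0.955 = 0.86

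This shows the mechanism only. Normal data would not trigger the fallback, so its size has to be judged on non-normal data.

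**Mann–Whitney against rank ANCOVA, both on change.** Simulation, 4,000 trials per setting, log-normal outcome, no site effect. Assumptions: treatment lowers the outcome by 0.5 SD on the log scale; log SD and ρ as shown. Power in percent:

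| Log SD | ρ | Mann–Whitney | Rank ANCOVA | Difference |
|---|---|---|---|---|
| 0.5 | 0.5 | 52 | 67 | 15 |
| 0.5 | 0.7 | 73 | 82 | 9 |
| 0.5 | 0.8 | 88 | 94 | 6 |
| 1.0 | 0.5 | 45 | 60 | 15 |
| 1.0 | 0.7 | 64 | 78 | 14 |
| 1.0 | 0.8 | 81 | 90 | 9 |

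With site in the rank model and a site SD between 0 and 0.3, the differences run from about 6 to 17 points.

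**Mann–Whitney against the ANCOVA actually planned (raw scale).** Same kind of data, 3,000 trials, no site effect. Power in percent, Mann–Whitney / planned ANCOVA:

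| Log SD | ρ = 0.5 | ρ = 0.7 | ρ = 0.8 |
|---|---|---|---|
| 0.8 | 47 / 58 | 68 / 73 | 82 / 83 |
| 1.0 | 47 / 52 | 64 / 63 | 81 / 75 |

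At log SD 0.5, Mann–Whitney is lower by about 15, 9 and 4 to 5 points. Under mild skew it loses; under strong skew and high correlation it gains.

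**Additive effects instead of proportional ones.** Six sites, 2,000 trials, ρ 0.3 to 0.9, site SD 0 or 0.3 outcome SDs. With heavy tails (t, 3 df): ANCOVA 81–84%, Mann–Whitney 77–94%, rank ANCOVA on change 91–95%. With log-normal errors: ANCOVA 81–84%, Mann–Whitney 91–99.7%, rank ANCOVA on change 98–99.8%. Rank ANCOVA is ahead or level throughout. Mann–Whitney ranges from about 7 points below planned ANCOVA to 18 above.

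**Log-scale ANCOVA.** In the log-normal setting with log SD 1 it reaches 75, 89 and 96% at ρ = 0.5, 0.7 and 0.8.

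**Type I error.** In null runs at ρ = 0.5 (1,000 trials each) the rejection rates across the three methods lay between 3.1% and 6.3%, close to the nominal 5% with no pattern of inflation.

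**The case against.** The strongest reply is that the sentence already names rank-based ANCOVA, and names it first. Mann–Whitney is only an example of a second branch, and the statistical analysis plan, which is not shown, may settle which is used. This limits the weight of the point but does not remove it. The protocol text positively permits an unadjusted test as an equal alternative, so the objection here is to something stated, not to detail left out.

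A reader might infer three stronger things, none of which the documents support.

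- **That the switch forfeits much of the power of the planned ANCOVA.** That impression comes from comparing Mann–Whitney with a log-scale ANCOVA, which the protocol does not plan. Much of that gap under strong skew is raw against log scale and would burden the planned ANCOVA as well. Against the planned analysis the sign of the difference depends on the degree of skew, the correlation and the form of the effect.
- **That the fallback contradicts the statement on site as a random effect.** That statement concerns statistical models, and Mann–Whitney is not a model; the secondary-outcome ANCOVA also does not name site. The mismatch is one of intent: randomization is stratified by site and clustering is meant to be handled, yet this test cannot do so.
- **That the fallback inflates false positives.** Each test holds its level, and nothing in the protocol says the choice would follow a look at the treatment comparison.

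It is also fair to say that baseline is not wholly ignored, since change subtracts it, and that the protocol does not state outright that Mann–Whitney would be run on change.

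**Conclusion.** The point holds in a limited form. The protocol permits, for continuous secondary outcomes that fail distributional checks, a test that adjusts for neither baseline nor the randomization stratum, next to one that can adjust for both. Compared with rank ANCOVA on change with baseline and site, the cost is roughly 6 to 17 points of power at 42 per arm.

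That range rests on assumptions the documents do not supply: log-normal data with log SD 0.5 to 1, a 0.5 SD reduction on the log scale, correlation 0.5 to 0.8 and site SD 0 to 0.3. It is not universal. If treatment raises the value, or the effect is additive on strongly skewed data, the gap is smaller and nearly closes in some settings at high correlation. Rank ANCOVA was not materially worse in any setting examined, so retaining the unadjusted option brings no evident benefit.

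The primary analysis has no such fallback and is unaffected. This is a worthwhile improvement to the secondary analyses, not a threat to the trial's main conclusion.

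**What to change.** In Statistical analysis, Secondary outcomes, delete the Mann–Whitney option and make rank-based ANCOVA with baseline and site the only fallback for continuous outcomes. Name site in the secondary ANCOVA too, so that the main and fallback analyses use the same terms.

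Optionally, list in advance the biomarkers expected to be skewed (hs-CRP, for example), analyse them by ANCOVA on the log scale with baseline and site, and report geometric mean ratios. That removes the distribution-triggered switch for those outcomes.

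The cost is a change of wording. No visit, measurement or sample size changes, and recruitment is planned to run to December 2027, so it can be settled well before database lock. The one trade-off is that outcomes on the log scale would be reported as ratios rather than differences.
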